### Intervention Description

This will be a longitudinal cohort study with 2 groups: the *intervention group*, which will receive the CH technology package at home, and the *usual care* group, which will not have any CH technology package at all. Selection to the CH or usual care group will be made by the PwD and their informal caregiver; thus, we will have adopter (intervention) and nonadopter (usual care) groups. The volunteer PwD-caregiver dyads will freely choose in which group they would like to participate as we acknowledge that this is a vulnerable population at an advanced age who might not be technology educated or might not feel comfortable with technology.

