#### Person With Dementia–Related Outcomes

The cognitive status level in the PwD will be measured using the *Mini-Mental State Examination* (MMSE) questionnaire. It is composed of 11 questions that cover 5 areas of cognitive function: orientation, registration, attention and calculation, recall, and language. The maximum score is 30, with a score of 23 or less being indicative of cognitive impairment. This is a quick and easy tool to administer directly to the PwD and is very useful when having to conduct it repetitively [19,20].

Behavioral and neuropsychiatric symptoms will be assessed with the short version of the *Neuropsychiatric Inventory Questionnaire* (NPI-Q). It is a way of providing a brief assessment of the PwD’s neuropsychiatric symptoms, which has been seen to be sensitive and reliable to capture changes in time related to delusions, hallucinations, agitation or aggression, depression or dysphoria, anxiety, elation or euphoria, apathy or indifference, disinhibition, irritability or lability, aberrant motor behavior, sleep and night-time behavior disorders, and appetite and eating disorders. It is based on responses of the caregivers who must also rate these symptoms in terms of frequency (how frequent those symptoms occur), severity (how severe and how much it affects the PwD), and distress (how distressing is it for them as caregivers and how much it may affect them). The NPI-Q does not have a cutoff score and, therefore, does not have a numeric scoring. Each domain is scored for frequency, severity, and associated caregiver distress, and the interviewer has to analyze them in those given terms [21-23].

Quality of life will be measured with the *Dementia Quality of Life* (DEMQOL) questionnaire, to gain an insight into their health-related quality of life. This is designed to work across dementia subtypes and care arrangements and is suitable for all the stages of the disease. It is composed of 2 questionnaires: (1) DEMQOL, a 28-item questionnaire answered by the PwD (self-reported quality of life) and (2) DEMQOL-Proxy, a 31-item questionnaire answered by the caregiver (PwDs’ caregiver- reported quality of life). Scored items are summed to produce a total score, with higher scores meaning a better health-related quality of life [24,25].

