### Data Analysis

Quantitative data from the participants’ quarterly assessments and daily monitoring data will be exported from the platform in the form of Excel documents. Descriptive statistics will be used to summarize the initial demographic data from our sample, which are obtained from the medical notes and the initial assessment examination (month 0), and for describing the findings of the questionnaires at each assessment point (months 3-12). Exploratory factor analysis will be conducted on the measured variables to identify the main constructs in our sample and how they correlate and interact with each other.

The main data collection points will be at 2 stages: months 0 and 12, as they will give us insight into the progress of the disease and the quality of life of the PwD and caregivers over 1 year, whereas interim data points will be available at 3, 6, and 9 months. Thus, the primary analysis of these repeated measures within each individual will be assessed using linear mixed models (LMMs). LMMs are suitable for correlated data such as these, and random intercepts and slopes can be allowed for individuals and subgroups. Change over time will be assessed, and differences between subgroups and interactions between covariates will be explored.

We also want to investigate changes in the scores between each assessment point (at 0, 3 6, 9, and 12 months). For this, analysis of variance or the equivalent nonparametric tests will be used. Regarding the assessments at months 3 to 9, these are the months when the technology is deployed at their homes and in which we can assess any potential impact derived from its use between the intervention and the usual care groups. This group comparison will be estimated by comparing the change in the volunteers’ scores between those 2 assessments (month 3 and month 9) using *t* tests or the correspondent nonparametric tests when appropriate.

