For this, a sample size calculation was derived using a rule of thumb for 20 observations for each dependent variable, so a sample size of 60 PwD-caregiver dyads is proposed. For the comparison of outcomes between the intervention and the usual care groups, caregiver burden and quality of life will be the primary outcome measure assessed at enrollment and at 6 and 12 months. Acknowledging that the PwD can deteriorate over time with a decline in their cognitive and functional status, we will use scores adjusted for baseline patient dependence and neuropsychiatric symptoms (analysis of covariance, ANCOVA model). We hypothesis a moderate between-groups effect size (*d*=0.5), so with 80% power and alpha=.05, a sample of 64 individuals in the intervention group and 64 in the usual care group is required for the *t* test. Adjusting for ANCOVA by sqrt (1-p2), where the p is the conservative correlation of 0.5 between repeated measures [39], results in a sample of 55 in each group. To account for dropout, 60 PwD-caregiver dyads will need to be recruited for each group. SPSS software (IBM Corp Version 24.0) will be used for this statistical analysis.

Analysis of the qualitative data obtained from the transcribed individual semistructured interviews will be analyzed using content analysis [40]. A guiding codebook will be used for this analysis, which will be created based on the topics examined in the interviews outlined above. The emerged categories will be organized, analyzed, and compared for generating themes. NVivo software version 12 for Macintosh (QSR International) will be used to organize the thematic analysis.

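### Dyads choose their own group, but the ANCOVA for the caregiver outcomes names two patient-side covariates only, listing neither the baseline outcome nor any caregiver characteristic

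*Protocol article*

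**What the plan says.** Intervention Description: "Selection to the CH or usual care group will be made by the PwD and their informal caregiver". The article itself labels the two groups adopters and nonadopters. The reason given is that some dyads may lack technology education or be uneasy with technology.

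Study Design, objective 1, asks how effective the platform is against usual care.

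Data Analysis describes three analyses that bear on the group comparison:

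- A linear mixed model over months 0 to 12, called the primary analysis of the repeated measures. It allows random intercepts and slopes. Covariates are mentioned only as something to explore.
- A month 3 to 9 comparison: "This group comparison will be estimated by comparing the change" in scores "between those 2 assessments (month 3 and month 9) using *t* tests or the correspondent nonparametric tests when appropriate". No covariate is named.
- An ANCOVA for caregiver burden and quality of life, measured at enrollment, 6 and 12 months: "we will use scores adjusted for baseline patient dependence and neuropsychiatric symptoms (analysis of covariance, ANCOVA model"). The reason given is decline in the patient: "Acknowledging that the PwD can deteriorate over time with a decline in their cognitive and functional status".

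The sample size in the same section starts at 64 per group for a t test (d = 0.5, 80% power, alpha 0.05). It is cut to 55 using a correlation of 0.5 between repeated measures and raised to 60 for dropout.

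**The concern.** Adopters and nonadopters are separated by comfort with technology. That plausibly goes with caregiver age, education, health literacy, mood and existing burden, all of which can bear on the caregiver outcomes. The stated ANCOVA adjusts for how dependent and how symptomatic the patient is. This answers a different worry, patient decline, and leaves the caregiver-side selection largely untouched.

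The section is also inconsistent with itself. A correlation between repeated measures of the outcome reduces the ANCOVA variance only if an earlier measurement of that outcome is in the model, and the covariate list does not include one.

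At stake is objective 1. A group difference in burden or quality of life could reflect who chose the platform rather than what the platform did, and selection could equally hide a benefit. A larger sample does not cure this.

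**Working it through.** **1. The plan's own figures.** Inputs from Data Analysis: d = 0.5, alpha 0.05 (two-sided, which is what reproduces the 64), power 80%, rho = 0.5.

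- Two-sample t test (noncentral t): n = 63.8, so 64 per group. Reproduced.
- Plan's ANCOVA factor: 64 × sqrt(1 − 0.5²) = 64 × 0.866 = 55.4, so 55. Reproduced.
- Dropout: 1 − 55/60 = 8.3% implied.

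**2. What 55 per group delivers.** The noncentrality is d / (SD × sqrt(2/55)), with outcome SD = 1.

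- Listed covariates explain no outcome variance: 0.5 / sqrt(2/55) = 2.62, power 74%.
- Baseline outcome in the model: residual SD = sqrt(1 − 0.25) = 0.866; 0.5 / (0.866 × sqrt(2/55)) = 3.03, power 85%.

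**3. Effect of a persistent group difference.** The article gives no baseline differences, so these inputs are assumptions: no true effect, 55 per group, two-sided 5%, rho = 0.5, and a group difference delta that is the same at baseline and follow-up. The two listed covariates are taken to remove none of it.

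- Follow-up score without the baseline outcome: bias = delta, SD = 1.
- Follow-up score adjusted for one baseline value: bias = delta × (1 − rho) = delta/2, residual SD = 0.866. This ignores the small variance inflation from covariate imbalance.
- Change score: bias = delta − delta = 0.

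| delta (SD) | No baseline outcome | One baseline value added | Change score |
|---|---|---|---|
| 0.2 | 18.0% | 9.2% | 5% |
| 0.3 | 34.5% | 14.7% | 5% |
| 0.4 | 54.7% | 22.5% | 5% |

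**4. Sensitivity to what the listed covariates do.** If they remove half the difference and explain 20% of the outcome variance, the bias is delta/2 with SD = sqrt(0.8) = 0.894. The rejection rates are then 8.9%, 14.1% and 21.3% for delta = 0.2, 0.3 and 0.4.

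**5. What the change-score test remains exposed to.** At rho = 0.5 the SD of change is sqrt(2 × (1 − 0.5)) = 1.

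- If the month 3 difference regresses to half its size, bias = delta/2 in absolute value: 8.1%, 12.2% and 18.0%.
- If the groups' natural trends over months 3 to 9 differ by 0.2, 0.3 or 0.4 SD: 18.0%, 34.5% and 54.7%.

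**The case against.** **The month 3 to 9 t test.** A reader might infer that this unadjusted test passes any pre-existing difference straight into the estimate. It does not. It compares changes, and a stable level difference cancels (5% in the table). Only differing trends and regression to the mean remain unaddressed. Replacing it with a month 9 ANCOVA would not be a plain improvement: with a stable difference, adjusting for one earlier value rejects more often than the change score does. With a regressing difference the order reverses.

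**The mixed model.** The article calls this the primary analysis of the repeated measures, and it already contains month 0. That stands, and it softens the point about the baseline outcome. It does not supply a confounder set.

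**Intention.** The 0.5 correlation and the enrollment measurement suggest that baseline adjustment was meant. That is plausible, so the fair description is an inconsistency between the sample size and the covariate list, not a proven decision to omit.

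**The NPI-Q.** The article says "The NPI-Q does not have a cutoff score and, therefore, does not have a numeric scoring", and a reader might conclude that neuropsychiatric symptoms cannot enter a model. The same paragraph says that each domain is scored for frequency, severity and caregiver distress. Domain scores can be used; the sentence is only awkward. Because the instrument is caregiver-rated and covers caregiver distress, it is also not wholly free of caregiver information.

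**Detail left to another document.** A full covariate list often sits in the analysis plan, which is not shown. Here, however, the article does name a set, with a reason, and that set does not fit self-selected groups. It also calls the design observational and labels the groups openly, which is to its credit but is not adjustment.

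**Conclusion.** The point holds for the ANCOVA. The stated adjustment addresses patient decline, not self-selection, for outcomes that belong to the caregiver, and it omits the baseline outcome on which the sample size takes credit.

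The size of any bias is unknown, and it may run either way. The rejection rates in the table depend on the assumed 0.2 to 0.4 SD persistent difference and, in the second column, on the listed covariates removing none of it. The baseline outcome alone does not bring the rate back to 5%, which is why caregiver factors are needed as well. The 74% against 85% power contrast rests on the plan's own d and rho; 74% is the case where the listed covariates explain nothing.

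The change-score t test is affected only in the narrower sense that it has no protection against differing trends or regression to the mean.

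**What to change.** - **ANCOVA:** add the baseline value of the outcome (Zarit or EQ-5D-5L) and prespecified caregiver factors: age, sex, relationship and co-residence, NVS and HADS. Keep patient dependence and neuropsychiatric symptoms, and state which NPI-Q score is used.
- **Linear mixed model:** enter the same caregiver factors. Month 0 is already a repeated measure there, so the baseline outcome need not be added. Where the group-by-time contrast is the target, include their interactions with time, because main effects adjust levels and not slopes.
- **Month 3 to 9 change comparison:** keep it. Beside it, report the group difference in month 0 to 3 change, before anyone has the package, as a check on prior trends. Give an estimate and confidence interval rather than a test: under the assumptions above, a 0.2 SD difference in change would be detected only 18% of the time.
- **Conclusion:** word it as an adjusted association between adopters and nonadopters.

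Cost: Zarit, EQ-5D-5L, NVS and HADS are in Table 1 at month 0, and caregiver demographics and social history are taken then. The article does not itemise these, so age, sex, relationship and co-residence are assumed to be among them. The ANCOVA loses 7 or 8 degrees of freedom (one each for the baseline outcome, age, sex, relationship, co-residence and NVS, and one or two for HADS) from 110 dyads. Time interactions in the mixed model cost a few more. The claim becomes more modest.

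### The ANCOVA sample size applies the residual-SD factor to n: at a correlation of 0.5, 55 per group gives about 85% power, not 80%, and only if the outcome's own baseline is a covariate

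*Protocol article*

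**What the plan says.** All of this is in the Data Analysis section of the protocol article.

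- The starting point is a standardised difference: "We hypothesis a moderate between-groups effect size (*d*=0.5". For an unadjusted t test at 80% power and alpha 0.05, the article puts the requirement at 64 per group.
- The reduction for covariate adjustment is given as "Adjusting for ANCOVA by sqrt (1-p2), where the p is the conservative correlation of 0.5 between repeated measures", and this "results in a sample of 55 in each group".
- Recruitment is then set: "To account for dropout, 60 PwD-caregiver dyads will need to be recruited for each group". No dropout rate is stated.
- The adjusted analysis is described as follows: "we will use scores adjusted for baseline patient dependence and neuropsychiatric symptoms (analysis of covariance, ANCOVA model". The primary outcomes are caregiver burden and quality of life, at enrolment and at 6 and 12 months. Their own enrolment values are not named as covariates.
- A paragraph earlier, a separate between-group t test is planned on the change "between those 2 assessments (month 3 and month 9", the period when the technology is in the home.

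**The concern.** Two things in the sample-size passage do not fit together.

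First, the factor is on the wrong scale. If a covariate has correlation ρ with the outcome, adjustment reduces the residual SD by √(1-ρ²) and the residual variance by 1-ρ². Required n is proportional to the variance, so it shrinks by 1-ρ². The article shrinks n by the square root.

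Second, the credit is taken for one covariate while others are named. A correlation between repeated measures is the correlation of the outcome with its own earlier value. It can be credited only if that earlier value is in the model. The covariates named are dependence and neuropsychiatric symptoms, and no correlation with burden or quality of life is given for them.

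At stake is whether a reader can tell what power the study has after losses. Follow-up lasts 12 months in people with dementia, and the consent section asks those whose cognitive score falls below 10 to leave, so the margin between recruited and needed will be used.

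**Working it through.** **Inputs from the article:** d = 0.5 (SD set to 1), alpha 0.05, 80% power, equal groups, ρ = 0.5, 55 per group after adjustment, 60 recruited. Sidedness is not stated, but 64 reproduces only as two-sided. Power is by the noncentral t distribution, with one degree of freedom removed for the covariate in the ANCOVA.

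**1. Reproduce the plan's figures.**
- Unadjusted t test, d = 0.5: 64 per group gives 80.1% (63 gives 79.5%). The 64 is right.
- 64 × √(1 - 0.25) = 64 × 0.866 = 55.4, stated as 55. So the square root was applied to n.

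**2. Use the factor for n.**
- 64 × (1 - 0.25) = 64 × 0.75 = 48.
- Equivalently, keep the SD factor and apply it to the SD: effective d = 0.5 / 0.866 = 0.577.

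| Completers per group | Power, ANCOVA on the outcome's baseline, ρ = 0.5 |
|---|---|
| 48 | 79.9% |
| 49 | 80.8% |
| 55 | 85.1% |
| 60 | 88.0% |

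So 49 is the smallest number that reaches 80%.

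**3. Loss that 60 recruited can absorb.**
- As written: (60 - 55)/60 = 8.3%.
- With 49 needed: (60 - 49)/60 = 18.3%.

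**4. ANCOVA with only the covariates named.** Let R be the multiple correlation of dependence and neuropsychiatric symptoms with the outcome. The article gives no value, so R is an assumption. Required n is about 64 × (1 - R²).

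| R (assumed) | 64 × (1 - R²) | Power at 55 |
|---|---|---|
| 0 | 64 | 73.8% |
| 0.3 | 58.2 | 77.8% |
| 0.375 | 55.0 | 80.0% |
| 0.4 | 53.8 | 80.9% |
| 0.5 | 48.0 | 85.1% |

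**5. The t test on month 3 to 9 change.** With equal variances, Var(change) = 2(1 - ρ) = 2 × 0.5 = 1 times the raw variance. At ρ = 0.5 there is no gain over the unadjusted t test: 64 completers are needed, 60 give 77.5% and 55 give 73.8%.

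**6. Allowance for self-selection.** The factor 1-ρ² assumes that the covariate is balanced between groups. If the groups differ at baseline by δ SD (δ assumed; none is given), the variance of the adjusted difference is multiplied by 1 + δ²/4.
- δ = 0.5: multiplier 1.0625, power 77.5% at 48 and 82.9% at 55.
- δ = 0.75: multiplier 1.141, power 74.6% at 48 and 80.2% at 55.

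**The case against.** The strongest reply is that the slip does no harm. For the analysis the calculation has in mind, 55 is more than enough, and the recruitment target would not change. That stands. A reader might infer from a wrong formula that the study is too small. For a baseline-adjusted ANCOVA the documents show the opposite.

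It can also be said that a correlation between repeated measures implies adjustment for the baseline outcome, and that a full covariate list is often left to the analysis plan. This has some force. But the article does list covariates for this ANCOVA, and the one that earns the reduction is not among them. Naming it removes the doubt.

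A reader might further infer that 55 fits none of the planned analyses. That cannot be shown. The linear mixed model, which the article calls the primary analysis, has no variance or correlation inputs from which to size it. For the ANCOVA with the named covariates, 55 is right if R is about 0.375.

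Finally, a reader might conclude that the month 3 to 9 t test can never reach 80%. That holds only at ρ = 0.5, a value the article itself calls conservative. With 60 completers per group it reaches 80% at ρ of about 0.53 (variance factor 2 × 0.47 = 0.94). Nor does the article attach its 80% to that test: the power statement belongs to the comparison at enrolment, 6 and 12 months. The shortfall is therefore a limit on what the figure covers, not a broken promise.

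**Conclusion.** The formula error is real and can be checked from the Data Analysis section alone: 55 arises only by multiplying n by √(1-ρ²), and it does not correspond to the stated 80% power at the stated correlation. For an ANCOVA that includes the outcome's baseline, the error is conservative: 49 completers per group suffice and 55 give about 85%. For the ANCOVA with only the covariates named, power at 55 is unknown. It lies below 80% for any multiple correlation under about 0.375, and is 73.8% at the bottom of the range.

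The point is moderate, because recruitment does not change. What changes is the stated power, the loss that can be tolerated, and the analysis to which both apply. The figures rest on d = 0.5, a two-sided test, equal group sizes and ρ = 0.5, with no baseline imbalance unless stated. The change-score figures also assume equal variances at the two visits.

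**What to change.** - Replace √(1-ρ²) by 1-ρ² as the factor for n.
- Keep 60 recruited per group, and restate along these lines: *55 completers per group give about 85% power (49 suffice for 80%, so 60 recruited allows about 18% loss) for an ANCOVA including the baseline value of the outcome, before any loss from baseline imbalance between self-selected groups.*
- Add the baseline value of the outcome to the covariates named for the ANCOVA.
- State that the figure does not cover the t test on month 3 to 9 change, which at ρ = 0.5 and equal variances has 77.5% power with 60 per group and 73.8% with 55.

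Lowering the target to 48 or 49 completers is not advised. 48 falls just short of 80%, and because dyads choose their own group, the margin up to 55 may be needed (step 6 of the working).

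The cost is two or three sentences. Recruitment, visits and data collection do not change.

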## Results

This 3-year funded study (2016-2019) is currently in its implementation phase. It is expected to finish by December 2019, and preliminary data results are expected to be submitted for publication by mid-2019. We believe that CH care approach can potentially change our current care model, moving from a previous passive and reactive approach to a more proactive and preventive model, utilizing self-management–based strategies, and enhancing caregivers’ involvement in the management of PwD’s health care in the home.

## Discussion

### Principal Findings

With this mixed methods study, we are addressing 2 spheres in the dementia informal home care. One is the invaluable quantitative health data collected from the PwD daily monitoring and the fact that, although the informal caregivers play the main role in PwD home care, there are many inconsistencies regarding the support provided to them. On the other sphere, the literature suggests that despite current trends in research claiming a user-centered design for increasing adoption and use [41], PwDs are not sufficiently involved in the design and development of CH solutions for dementia home care. Therefore, PwDs’ and their informal caregivers’ needs and perspectives are not considered and integrated into the product designed, so they are not customized for them [42,43]. Consequently, because of the created necessity of understanding the needs and attitudes of PwD and their informal caregivers regarding CH technology, we have included a qualitative approach to address these deficits outlined here. We hope that our combined results from both domains, qualitative and quantitative, will bring new perspectives on how to design and conduct CH research with PwDs and their informal caregivers.

